### 2.7. Sample Size Calculation

Considering the attrition rate, we will recruit 260 students to obtain 200 study completers. A total of two-hundred participants will allow to detect an effect size of at least d = 0.40, fixing a power (1 − β) of 80%, and an alpha of 0.05 (two-tailed) in a between group comparison (e.g., comparing the two treatments). This sample size is similar to Harrer et al. [25]. The effect size is estimated considering a recent meta-analytic review for Internet-based stress interventions which reports effect sizes ranging between d = 0.32 and d = 0.64 [81].

Frequentist and Bayesian approaches have their own advantages and drawbacks in data analysis. We will adopt both to provide robust evidence to the specific statistical approach.

We conducted a Bayes Factor Design Analysis (BFDA) [82] (i.e., the counterpart of power analysis in the Bayesian world) to estimate the Bayesian analysis sensitivity, given the sample size of 200 people. We simulated 10,000 results, fixing the Bayes Factor (BF) decision boundary at 10, and an estimated effect size for a true H1 equal to d = 0.40. The BFDA simulation was performed for a default prior (i.e., a Cauchy distribution with a scale = 0.707) and an informative prior (i.e., a t distribution with μ = 0.35, df = 3, r = 0.102), considering true H0 (i.e., d = 0) and H1 (d = 0.40). Given those parameters, we estimate to surpass the decision boundary for H1 in 87.8% adopting the default prior and 93.8% of the case adopting the informed prior. In the case of a true H0, the decision boundary is surpassed in 45.5% and 62.2% of the cases adopting the default or the informed prior, respectively. The design is robust to the misleading evidence, showing a false positive evidence rate of 0.002 and 0.006 adopting the default or the informed prior. No false negative evidence has been observed over 10,000 simulations with any of the two priors. In the case of inconclusive evidence, we will increase the sample size until the BF decision boundary is surpassed (BF > 10) in either one of the two directions supporting H1 or H0.

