### 2.8. Statistical Methods

Statistical analyses will be conducted adopting both a frequentist and a Bayesian approach to provide robust evidence favoring or against the intervention.

The main study outcome is to verify the effectiveness of the intervention: this would be verified by a T0 to T1 delta different from 0. Additionally, we will test the effectiveness of the IB-MAI against the CC group comparing the two T0 to T1 deltas. We will use a series of *t*-tests and its Bayesian [83] corresponding test.

Stability over time will be verified with a mixed ANOVA using the T1, T2 and T3 datapoints as within-subject measures and group (IB-MAI versus CC) as a between-subjects factor. We will use “classic” (i.e., frequentist) ANOVA and its corresponding Bayesian version [84] for each primary and secondary outcome measure.

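### The Bayes-factor stopping rule has no verdict for control being better, and with the informed prior at 100 per arm an H0 verdict is likelier under small-to-moderate harm than under no effect

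*Protocol article*

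**What the plan says.** Section 2.7 of the protocol article plans a frequentist comparison with "an alpha of 0.05 (two-tailed) in a between group comparison", then a Bayes factor design analysis "to estimate the Bayesian analysis sensitivity, given the sample size of 200 people". Two priors for the effect under H1 are given. One is "a default prior (i.e., a Cauchy distribution with a scale = 0.707"). The other, centred on benefit, is "an informative prior (i.e., a t distribution with μ = 0.35, df = 3, r = 0.102"). Neither is described as truncated or one-sided. The simulation was run "considering true H0 (i.e., d = 0) and H1 (d = 0.40"), with a boundary of 10; no negative effect was simulated.

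The printed rates, default then informed prior, are 87.8% and 93.8% for passing the H1 boundary at d = 0.40, 45.5% and 62.2% for passing the H0 boundary at d = 0, and 0.002 and 0.006 for false positive evidence. If the evidence is inconclusive, the sample grows "until the BF decision boundary is surpassed (BF > 10) in either one of the two directions supporting H1 or H0". Those are the only two end states.

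Section 2.8 runs both approaches "to provide robust evidence favoring or against the intervention". It names t-tests and their Bayesian counterpart but does not restate a prior or a direction.

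**The concern.** A Bayes factor compares H0 with the particular alternative it was given. If nearly all of that alternative lies on benefit, a large BF for H0 says that zero fits better than the expected benefit. It does not say that the arms are equal, because data that lean towards control also fit zero better than they fit a benefit. A rule with only the labels H1 and H0 has nowhere to put a result that favours control.

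At stake are the label on such a result and the decision to end recruitment on it. The primary outcomes in section 2.6.1 include a suicide-risk scale, so modest deterioration labelled as support for no effect would be a material misreading.

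**Working it through.** **Inputs.** From section 2.7: both priors, the boundary of 10, 200 people and the two simulated effects. From section 2.3: 1:1 allocation, hence 100 per arm. Positive d favours the app.

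**Formula.** For n per arm and ν = 2n - 2, BF10(t) = ∫ f(t; ν, δ√(n/2)) π(δ) dδ ÷ f(t; ν, 0), where f is the noncentral t density and π the prior; BF01 = 1/BF10. The t values at which BF01 or BF10 equals 10 are found numerically. The probability of each verdict follows from the noncentral t with noncentrality d√(n/2).

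**Step 1: the plan's own figures.** The frequentist part reproduces: 100 per arm gives 80% power at d = 0.40. The Bayesian rates do not reproduce at 100 per arm:

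| Prior | n per arm | H1 rate at d = 0.40 | H0 rate at d = 0 |
|---|---|---|---|
| Default, printed | – | 87.8% | 45.5% |
| Cauchy 0.707, symmetric | 100 | 43% | 0% |
| Cauchy 0.707, d > 0 | 100 | 53% | 26% |
| Cauchy 0.707, d > 0 | 200 | 88.0% | 44.7% |
| Informed, printed | – | 93.8% | 62.2% |
| Informed, untruncated | 100 | 70% | 38% |
| Informed, untruncated | 200 | 93.7% | 63.4% |

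The symmetric Cauchy reaches its largest BF01 at t = 0: 6.5 at 100 per arm and 9.0 at 200. It cannot pass 10 at either size, so a 45.5% H0 rate is impossible with the prior as written. Of the variants tried, only the d > 0 version at 200 per arm comes close.

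**Step 2: where the informed prior puts its mass.** P(δ < 0) = P(T₃ < -0.35/0.102) = P(T₃ < -3.43) = 2.1%, leaving about 98% on benefit.

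**Step 3: informed BF01 at 100 per arm.**

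| t | BF01 | two-sided p |
|---|---|---|
| 0 | 7.4 | 1 |
| -0.5 | 12.3 | 0.62 |
| -1.0 | 16.1 | 0.32 |
| -1.5 | 16.0 | 0.14 |
| -2.0 | 11.8 | 0.047 |
| -2.1 | 10.7 | 0.037 |

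BF01 exceeds 10 for t from about -2.17 to -0.27 and nowhere else. Below t of about -4.23, BF10 exceeds 10, so the verdict becomes H1 with a negative estimate.

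**Step 4: probability of the H0 verdict by true d, single look.**

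| True d | Informed, 100/arm | Informed, 200/arm | Default d > 0, 100/arm | Default d > 0, 200/arm |
|---|---|---|---|---|
| 0 | 38% | 63% | 26% | 45% |
| -0.1 | 59% | 80% | 53% | 81% |
| -0.2 | 64% | 56% | 78% | 97% |
| -0.3 | 48% | 21% | 93% | 99.8% |
| -0.4 | 25% | 3% | 99% | 100% |

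Example: at d = -0.2 and 100 per arm the noncentrality is -0.2 × √50 = -1.41, and P(-2.17 < t < -0.27) = 64%. With the informed prior at 100 per arm, the BF passes the H1 boundary with a negative estimate in about 9% of trials at d = -0.4 and 25% at d = -0.5.

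**Step 5: with extension.** The article gives no look schedule. With looks assumed every 25 per arm from 100 to 600, the informed BF ends at H0 in 93% of trials at d = 0, 98% at -0.1, 85% at -0.2, 57% at -0.3 and 30% at -0.4. At -0.3 a further 42% end at H1 with a negative estimate. With looks every 10 per arm and a cap of 1,000 per arm, the H0 figures at -0.2 and -0.3 are 87% and 61%. The d > 0 default BF ends at H0 in 100% at d = -0.2 and beyond.

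**The case against.** A reader might infer that both Bayes factors are built solely against benefit and that harm will be reported as no effect. The documents do not support that.

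- The default prior as printed is symmetric. Under it, harm goes to H1 with a negative sign and never to H0 at the planned size. Its one-sidedness is inferred from printed rates, and the match needs 200 per arm although the text says 200 people.
- The informed prior is not blind to harm. Its H0 rate falls as harm grows, and the BF crosses to H1. At 200 per arm the H0 rate peaks at 80% near d = -0.09, and at d = -0.2 it is already below its value at d = 0. After extension, too, H0 is likelier than under no effect only for very small harm.
- Every Bayesian test is paired with a two-tailed t-test. For the informed BF at 100 per arm, an H0 verdict together with p < 0.05 against the app occurs in only 6% of trials at d = -0.2, 8% at -0.3 and 6% at -0.4. Nothing says a result favouring control would be reported as H0.
- The priors are stated for the design analysis. Section 2.8 leaves the analysis priors open, and an analysis plan may fix them.

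All four points stand as limits on the claim. They leave these facts in place: the printed H0 rate contradicts the printed default prior, the extension rule depends on the BF alone, it has no outcome for control being better, and no negative effect was examined.

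**Conclusion.** The concern holds in a limited form. With the informed prior as printed and 100 per arm, the H0 boundary can be passed only when control is ahead, and it is passed more often at d = -0.1 to -0.3 (59%, 64%, 48%) than at d = 0 (38%). At d = -0.4 this falls to 25%, and some trials instead pass the H1 boundary with a negative estimate, a label that is no more apt.

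If the default BF is one-sided, as its printed rates imply, its H0 rate rises steadily with harm and includes every result that is significant against the app.

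The conclusion assumes that the design priors are also the analysis priors (no others are named), that there are 100 completers per arm at the first look, and, for the extension figures, the assumed look schedules. It is a correctable gap in the stopping rule and in the reading of BF01, not evidence that the sponsor intends to hide harm.

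**What to change.** In sections 2.7 and 2.8:

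1. State for each Bayes factor whether it is one- or two-sided, and correct either the description of the default prior or its printed rates, including whether 200 means people or per arm.
2. Describe BF01 from the informed or a one-sided prior only as evidence against the specified benefit.
3. For each outcome, add a BF for d < 0 against d = 0 and a 95% interval for the between-arm difference.
4. When these favour control, do not declare H0, stop recruitment for H0 or claim support for a benefit hypothesis; report the result as favouring control. Fix the threshold in advance and do not use the sign alone, because at 100 per arm every informed H0 verdict has control ahead.
5. Add negative d to the design analysis.

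The cost is a few sentences, a rerun of the simulation, one more BF and one interval per outcome, and somewhat fewer H0 verdicts.

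Requiring the symmetric Cauchy for every H0 stop is not advised. It first reaches BF01 = 10 at about 250 per arm, that is 500 completers, or 500 × 260/200 = 650 recruits at the plan's attrition, so no H0 stop would be possible at the planned size.

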### 2.3. RCT Design

This study will be conducted in accordance with the Consolidated Standards Of Reporting Trials (CONSORT) checklist for the RCT design [34]. Participants will be randomly assigned following blind simple randomization procedures when they complete the baseline assessment (randomization sequence under computer control adopting computerized random numbers) to 1 of 2 treatment groups (see Figures S1 and S2 for the study design and assessments). We only keep the 1:1 ratio constraint at the 260th participant, meaning that when one group reaches 130 participants, all the remaining volunteers (up to the total of 260) will be allocated to the other group. Students will be randomized to IB-MAI or CC. Participants in the intervention condition will receive an 8-week unguided IB-MAI program, i.e. MindBlooming. Participants in the CC condition will access websites with information about their specific areas of distress identified at baseline. Participants will be assessed with repeated measures (baseline, 8 weeks, 12 weeks, and 24 weeks). The RCT participants’ flow is presented in Figure 2.

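### The Bayes factor design figures fit 200 participants per group, but the trial plans 200 in total, so the stated Bayesian sensitivity is far too high

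*Protocol article*

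**What the plan says.** All the figures are in section 2.7 of the protocol article.

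- **Sample size.** The trial expects dropout: "we will recruit 260 students to obtain 200 study completers". Section 2.3 fixes two arms at 1:1, since "when one group reaches 130 participants, all the remaining volunteers (up to the total of 260) will be allocated to the other group". The 200 completers are therefore about 100 per group.
- **Frequentist statement.** "A total of two-hundred participants will allow to detect an effect size of at least d = 0.40". This is for 80% power with a two-sided 5% test between the arms.
- **Bayesian statement.** A Bayes Factor Design Analysis (BFDA) was run "to estimate the Bayesian analysis sensitivity, given the sample size of 200 people". Evidence counts as decisive when the Bayes factor passes 10, and the true effect is taken as 0.40 or 0. The priors are a Cauchy with scale 0.707 (default) and a t with location 0.35, scale 0.102 and 3 df (informed).
- **Results.** With d = 0.40, "we estimate to surpass the decision boundary for H1 in 87.8% adopting the default prior and 93.8% of the case adopting the informed prior". With d = 0, "the decision boundary is surpassed in 45.5% and 62.2% of the cases adopting the default or the informed prior, respectively". False-positive evidence is given as 0.002 and 0.006, and no false negatives were seen in 10,000 runs under either prior.
- **Consequence.** If the evidence is inconclusive, recruitment continues until the Bayes factor passes 10 in one direction or the other.

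**The concern.** The frequentist and Bayesian statements describe the same 200 people, yet a much stricter evidence threshold is reported as being met more often than p < 0.05. That pattern suggests 200 was entered as the number per group.

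Two things are at stake. Section 2.8 gives the Bayesian test equal standing with the frequentist one, so its sensitivity is a design property that readers will rely on. The same rates also show how often the rule for enlarging the sample would come into play. If they are too high, the need for extension is understated.

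**Working it through.** **Inputs.** From section 2.7: 200 completers, d = 0.40 or 0, boundary 10 (1/10 for H0), the two priors, 10,000 simulations. From section 2.3: 1:1 allocation, hence n = 100 per group and 198 df. Prior direction is not stated, so both options were run.

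**Step 1: the frequentist figure reproduces at 100 per group.** The noncentrality is d·√(n/2) = 0.40·√50 = 2.83 and the two-sided 5% critical value is 1.97. Power is about Φ(2.83 − 1.97) = Φ(0.86) ≈ 0.80 (80.4% from the noncentral t). The design figure of 200 is thus a total.

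**Step 2: where BF > 10 falls on the t scale.** The Bayes factor is the noncentral-t likelihood averaged over the prior, divided by the central-t density. Solving BF = 10 at 100 per group, with P ≈ Φ(2.83 − threshold):

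| Prior | t needed | P(BF > 10), d = 0.40 | Stated |
|---|---|---|---|
| Default, directional | 2.75 | 53% | 87.8% |
| Default, two-sided | 3.01 | 43% | 87.8% |
| Informed, either direction | 2.29–2.30 | 70% | 93.8% |

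Every threshold exceeds 1.97. A harder hurdle on the same statistic cannot be passed 87.8% or 93.8% of the time when the easier one is passed 80% of the time.

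**Step 3: full simulation (2,000,000 t values per scenario).**

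| | Stated | 100 per group | 200 per group |
|---|---|---|---|
| Default, BF > 10, d = 0.40 | 87.8% | 53.5% directional, 43.1% two-sided | 88.0%, 82.4% |
| Informed, BF > 10, d = 0.40 | 93.8% | 70.5% directional, 70.2% two-sided | 93.9%, 93.8% |
| Default, BF < 1/10, d = 0 | 45.5% | 26.2%, 0% | 44.7%, 0% |
| Informed, BF < 1/10, d = 0 | 62.2% | 43.3%, 37.6% | 66.5%, 63.4% |
| Default, false positive | 0.002 | 0.003 | 0.002–0.003 |
| Informed, false positive | 0.006 | 0.011–0.012 | 0.007 |

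Under the two-sided default prior the largest possible Bayes factor for H0 at 100 per group is 6.5 (at t = 0), so H0 can never be supported at the chosen boundary. A separate run on 10,000 raw data sets per scenario agreed. Using all 260 randomised (130 per group, directional priors) gives about 68% and 82% under d = 0.40, still well short.

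**Step 4: a check that uses no prior.** If BF > 10 corresponds to an upper-tail cut-off, the stated false-positive rate and the stated success rate together fix the noncentrality as z(1 − false positive) + z(success).

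- Default: 2.88 + 1.17 ≈ 4.04, so n = 2·(4.04/0.40)² ≈ 204 per group.
- Informed: 2.51 + 1.54 = 4.05, so n ≈ 205 per group.

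A design with 100 per group has 2.83. The stated rates fit 200 per group, where 0.40·√100 = 4.0.

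**Step 5: false negatives.** At 100 per group the informed prior gives 0.00095–0.00135, so about 10 to 14 are expected in 10,000 runs. Seeing none has probability below 0.0001 (e^−9.5 at most). At 200 per group about 1.3 to 1.6 are expected, and none is unremarkable.

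**Step 6: how often the result is inconclusive at N = 200** (100% minus conclusive results in either direction).

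| | Implied by the text | At 100 per group |
|---|---|---|
| d = 0.40, default | 12.2% | 46.5% directional, 56.9% two-sided |
| d = 0.40, informed | 6.2% | 29–30% |
| d = 0, default | 54.3% | 73.5% directional, 99.7% two-sided |
| d = 0, informed | 37.2% | 55.5% directional, 61.3% two-sided |

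**The case against.** **The cause is inferred.** The BFDA paragraph does not name its test. Section 2.8 puts a within-arm change from T0 to T1 first and the between-arm comparison second. A one-sample test on 100 people (one arm) gives similar rates: 87.1% and 93.5% under d = 0.40, and 44.7% and 63.3–66.4% under d = 0. This stands as a caution about origin. It fits slightly less well: 87.1% is about two Monte Carlo standard errors from 87.8%, against under one for 88.0%. It would also describe 100 people rather than the stated 200, and would say nothing about the between-group comparison.

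**The match at 200 per group is imperfect.** The informed figure under H0 is 62.2% as stated, against 63.4% at best. With a standard error near 0.5 points that is about 2.5 standard errors, and the directional value of 66.5% is much further off. The best overall fit pairs a directional default prior with an untruncated informed one. This is fair, but the values at 100 per group (37.6–43.3%) are not remotely close.

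**The two-sided default prior was probably not used.** It gives 0% under H0 even at 200 per group, so the printed 45.5% points to a directional prior. For the default prior the main comparison is therefore 53% against 87.8% and 26% against 45.5%. The two-sided values still matter because the article leaves direction unstated.

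**The target of 200 does not rest on the BFDA.** This is true: it rests on the frequentist calculation, which is sound, and the article itself reports frequent inconclusive results under H0. That limits the consequences but does not make the printed rates correct.

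**Conclusion.** The concern holds. For the between-group test at 200 completers in total, the stated chance of BF > 10 at d = 0.40 is too high by about 34 points under a directional default prior (87.8 − 53.5), 45 under a two-sided one (87.8 − 43.1), and 23 under the informed prior (93.8 − 70.5). Under H0 the overstatement is about 19 points (45.5 − 26.2) or the full 45.5 for the default prior, and 19 to 25 points for the informed prior. False-positive evidence under the informed prior is roughly double the stated 0.006.

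These sizes assume equal groups of 100, a standard two-sample t-test and the priors as printed. That the figures are wrong for this design does not depend on prior direction, on how the error arose, or on whether 200 or 260 participants are analysed. That 200 was entered per group is the best explanation, not a certainty.

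**What to change.** Rerun the BFDA for the two-sample comparison with 100 per group. State the test, the number per group and whether each prior is directional. Then replace the printed rates:

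- BF > 10 at d = 0.40: about 53% (directional) or 43% (two-sided) for the default prior, and about 70% for the informed prior.
- BF < 1/10 at d = 0: about 26% or 0% for the default prior, and about 38–43% for the informed prior.
- False-positive evidence: about 0.003 and 0.011. The statement that no false negatives occurred should be replaced by the new counts.

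The text should also say plainly that, at 200 completers, an inconclusive Bayes factor is a common outcome even if d = 0.40, so that the extension rule is planned for on realistic odds. If a two-sided default prior is intended, say that H0 cannot reach the boundary at this sample size.

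The cost is minutes of simulation and a corrected paragraph, with less favourable figures. Restating them requires no extra participants, and the frequentist calculation is unaffected.

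### The false positive evidence rates of 0.002 and 0.006 are single-look rates, but the plan extends enrolment until the Bayes factor passes 10, which makes them several times higher

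*Protocol article*

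**What the plan says.** Section 2.7 (Sample Size Calculation) describes the Bayesian design analysis as run "to estimate the Bayesian analysis sensitivity, given the sample size of 200 people". It uses 10,000 simulations, a Bayes factor boundary of 10, true effects d = 0 and d = 0.40, and two priors: Cauchy with scale 0.707, and t with location 0.35, scale 0.102 and 3 df. Under d = 0.40 the boundary for H1 is crossed in 87.8% (default) and 93.8% (informed) of runs. Under d = 0 the boundary is crossed in 45.5% and 62.2%.

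The section then states: "The design is robust to the misleading evidence, showing a false positive evidence rate of 0.002 and 0.006" for the two priors, and adds "No false negative evidence has been observed over 10,000 simulations with any of the two priors".

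The last sentence of the paragraph says that, if the evidence is inconclusive, "we will increase the sample size until the BF decision boundary is surpassed (BF > 10) in either one of the two directions". No error rates are given for that rule.

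**The concern.** A frequentist error rate depends on the stopping rule. The rates of 0.002 and 0.006 describe one look at one sample size. The extension rule adds further looks for every trial that is inconclusive at the first, and under H0 each look is another chance to cross the H1 boundary by luck.

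By the article's own figures this is a common path. A null trial would be inconclusive in about 100 − 45.5 = 54.5% of cases with the default prior and 100 − 62.2 = 37.8% with the informed prior.

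At stake is how a positive result will be read. A reader would attach a false positive chance of 0.2% to 0.6% to a Bayes factor above 10 in favour of the app, and the planned procedure does not have that property. Section 2.8 plans such tests for a series of outcomes, so the understatement recurs for each test to which the rule is applied.

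**Working it through.** **Inputs.** All are from section 2.7 unless noted.
- Priors, boundary and true effects as listed above; H0 is supported when BF10 < 1/10.
- "we will recruit 260 students to obtain 200 study completers".
- Allocation 1:1 (section 2.3: "We only keep the 1:1 ratio constraint at the 260th participant"), so 200 completers are taken as 100 per arm.
- Frequentist basis: "an alpha of 0.05 (two-tailed) in a between group comparison", power 80%, d = 0.40.

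**Step 1: what 200 means in the frequentist calculation.** A two-sample t-test with 100 per arm, d = 0.40 and two-sided 0.05 has power 0.804. So 200 is the total there.

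**Step 2: reproduce the printed Bayesian figures at a single look.** For n per arm,

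BF10(t) = ∫ f(t; 2n − 2, δ√(n/2)) π(δ) dδ ÷ f(t; 2n − 2, 0),

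where f is the noncentral t density and π the prior on the standardised effect δ.

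| Single look | P(BF10 > 10 given d = 0.40) | P(BF10 < 1/10 given d = 0) | P(BF10 > 10 given d = 0) |
|---|---|---|---|
| Printed, default | 0.878 | 0.455 | 0.002 |
| 200 per arm, default, one-sided | 0.880 | 0.447 | 0.0025 |
| Printed, informed | 0.938 | 0.622 | 0.006 |
| 200 per arm, informed, two-sided | 0.938 | 0.634 | 0.0071 |

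At 100 per arm the figures do not reproduce. P(BF10 > 10 given d = 0.40) is 0.43 (two-sided) or 0.53 (one-sided) for the default prior and 0.70 for the informed prior, and the false positive rates are 0.003 and 0.011.

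Two things follow. The printed rates are single-look rates, since the simulation leaves many trials undecided, and a run-until-decided design would leave almost none. Separately, they match 200 per arm and not 200 in total. Because of that mismatch, both starting sizes are carried forward.

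**Step 3: apply the extension rule under d = 0.** Each setting has 100,000 simulated trials with normal outcomes. The first look is at 100 or 200 per arm. Blocks of 1, 10, 30 or 50 per arm are then added until BF10 > 10 or BF10 < 1/10. A computing cap of 20,000 per arm leaves at most 0.04% undecided. Block sizes are an assumption.

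| First look | Prior | First-look rate | Rate with extension | Ratio to printed rate |
|---|---|---|---|---|
| 100 per arm | default | 0.003 | 0.014–0.025 | 7–13 |
| 100 per arm | informed | 0.011 | 0.027–0.044 | 4.5–7.4 |
| 200 per arm | default | 0.002 | 0.011–0.017 | 5.5–8.6 |
| 200 per arm | informed | 0.007 | 0.016–0.025 | 2.7–4.1 |

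The upper end of each range belongs to the closest spacing. A smaller run (20,000 trials, looks every 10 or 50 per arm, cap 2,000 per arm) gave 0.012–0.021, 0.027–0.038, 0.009–0.014 and 0.018–0.020 in the same order.

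**Step 4: isolate the effect of the extension.** Dividing by the printed rates mixes the extension with the N mismatch of step 2. For example, the informed single-look rate at 100 per arm is already 0.011 ÷ 0.006 ≈ 1.9 times the printed value with no extension at all. Dividing by the first-look rate at the same starting size removes this and gives about 4 to 8 for the default prior and 2 to 4 for the informed prior.

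**The case against.** The article labels the analysis as conditional on 200 people, mentions the extension only afterwards, and does not say that the error rates justify it. A Bayes factor keeps its evidential meaning under optional stopping. The highest rate found, 0.044, is below the plan's own alpha of 0.05. Look schedule and maximum N may sit in a fuller document.

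Much of this stands, and it limits the point. It does not remove it. The article chose to report a frequentist error rate and to call the design robust on that basis, and the design it then describes has a different rate in every setting tried.

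Several stronger readings are tempting but not supported:
- **A fixed multiplier, or fixed replacement values.** A reader might divide the 100-per-arm results by the printed rates and quote a single factor. The factor depends on look spacing, which is not given, and absorbs the N mismatch.
- **That an inconclusive first look is the usual result under H0.** With the informed prior the printed figure implies only 37.8%.
- **That the extension falsifies the false negative statement.** The article reports that none occurred in 10,000 runs; it does not claim a zero rate. With the informed prior at d = 0.40 from 200 per arm, the rate is about 0.015% at a single look and 0.013–0.023% with extension, which is compatible with none observed. From 100 per arm it is 0.10% at a single look and about 0.13–0.3% with extension, so a good part comes from the starting size. With the two-sided default prior none occurred in 60,000 trials from either start.

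**Conclusion.** The point holds in this form: 0.002 and 0.006 are single-look, fixed-N rates, and the robustness statement rests on a design that will not be run. Under the extension rule the per-test false positive rate is about 0.01 to 0.025 (default) and 0.016 to 0.044 (informed).

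The direction does not depend on the assumptions; the size does. It rests on normal outcomes, equal arms, a first look at 100 or 200 per arm, looks every 1 to 50 per arm, and no effective maximum N.

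A reader might infer that the false positive rate is out of control. It is not: each test stays below 0.05. The fault is a printed operating characteristic that is several times too favourable for the planned procedure.

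**What to change.** Re-run the design analysis as the sequential design actually planned, with both priors. State the first-look N per arm, the look spacing, any maximum N, and which outcome and prior govern the decision to continue. Replace 0.002 / 0.006 and the robustness sentence with the resulting false positive and false negative rates. In the same step, say whether 200 is the total or the number per arm, since the printed figures match the latter.

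Alternatively, drop the extension and report fixed-N rates for the N actually planned.

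The cost is one repeat of an existing simulation and a few reworded sentences. The downside is a slightly less favourable stated error rate.

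### The t-tests are justified for a fixed 200 completers, but the Bayes factor may extend the sample and the plan does not say which sample gives the frequentist result

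*Protocol article*

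**What the plan says.** Protocol article, 2.7, frequentist sizing: "we will recruit 260 students to obtain 200 study completers". That number "will allow to detect an effect size of at least d = 0.40", with power "of 80%, and an alpha of 0.05 (two-tailed) in a between group comparison". The effect is drawn from a meta-analytic review reporting "effect sizes ranging between d = 0.32 and d = 0.64".

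The same section reports a Bayes factor design analysis for 200 people with a boundary of 10 and two priors: a default Cauchy with scale 0.707, and an informed t prior (location 0.35, df 3, scale 0.102). It closes with the extension rule: "In the case of inconclusive evidence, we will increase the sample size until the BF decision boundary is surpassed (BF > 10", for H1 or H0. It gives no maximum size, look schedule, deciding outcome or deciding prior.

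Protocol article, 2.8: "Statistical analyses will be conducted adopting both a frequentist and a Bayesian approach to provide robust evidence favoring or against the intervention". The changes from T0 to T1 are compared by t-tests and their Bayesian counterparts. Nothing there ties the t-tests to the planned 200 or adjusts them after an extension.

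Protocol article, 2.3, describes allocation for a trial that ends at 260: "We only keep the 1:1 ratio constraint at the 260th participant".

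**The concern.** The two rules in 2.7 do not fit together. Alpha 0.05 and 80% power are properties of one t-test at a size fixed in advance. If the Bayes factor on the same data decides whether recruitment goes on, the final size depends on the results, and a t-test run on whatever sample is then available is a different procedure.

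The mechanism is simple. Under a true moderate effect, recruitment tends to stop when the running estimate is high enough to pass the boundary for H1, so the estimate at stopping is on average too large. Close to the null, stopping for H0 pulls the other way.

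The plan uses both approaches so that the conclusion does not rest on one statistical method. That purpose is weakened if the Bayes factor also decides when the frequentist data set is complete. This point concerns the frequentist estimate, alpha and any interval. It does not concern the Bayesian rates of misleading evidence.

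**Working it through.** **Step 1. The plan's own size.** Inputs from 2.7: d = 0.40, two-sided alpha 0.05, power 80%. Per arm, n = 2(1.960 + 0.842)² / 0.40² = 2 × 7.85 / 0.16 = 98.1, so 99 per arm (198 in total). At 100 per arm the normal approximation gives power Φ(0.40 × √50 − 1.960) = Φ(0.868) = 80.7%; the exact t-test gives 80.4%. The 200 completers reproduce, for a single test at that size.

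**Step 2. How often the sample would be extended.** From the figures in 2.7, at d = 0.40: 100 − 87.8 = 12.2% (default prior) and 100 − 93.8 = 6.2% (informed). Under no effect: 100 − 45.5 = 54.5% and 100 − 62.2 = 37.8%, less any false-positive crossings. Simulation at 100 per arm gives more at d = 0.40: 56–58% (default prior, two-sided), 46–47% (default, one-sided) and about 30% (informed).

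**Step 3. The t-test under the extension rule.** Assumptions, because the article gives none:
- first look at 100 per arm, then a look after every 1, 10 or 30 per arm
- stop at a Bayes factor above 10 or below 1/10, with truncation at 2,500–3,000 per arm
- one outcome, which drives the extension
- default prior (two-sided or one-sided) or informed prior

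At the end, the ordinary estimate and a nominal 95% interval are computed as if the size had been fixed. The ranges below span the priors and look schedules.

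| True d | Mean estimate | Coverage of nominal 95% interval |
|---|---|---|
| 0 | 0 (two-sided); −0.03 to −0.06 (one-sided or informed) | 93–98% |
| 0.10 | 0.08–0.10 | 90–95% |
| 0.20 | 0.22–0.25 | 89–95% |
| 0.30 | 0.33–0.35 | 94–97% |
| 0.40 | 0.42–0.44 | 96–97% |

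Relative bias, from unrounded means, is about +4% to +9% at d = 0.40 (for example 0.416 / 0.40 − 1 = 4%) and about +11% to +23% at d = 0.20. At d of 0.10 or less there is no upward bias.

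The lowest coverage over all true effects tried is about 90–91% (default two-sided), 88–89% (default one-sided) and 87–89% (informed). These minima occur near d = 0.04–0.08 or d = 0.18–0.26. For d = 0.32–0.44, coverage is about 95–97%.

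**Step 4. Type I error.** The two-sided t-test at the stopping size rejects a true null in 2–3% (default two-sided), about 5–6% (default one-sided) and 6–7% (informed). If significance at either the 200-completer look or the final look were counted, the rate would be about 6–9%.

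**Step 5. Comparison.** At a fixed 200 completers the same t-test has 5% type I error, an unbiased estimate and 95% coverage.

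**The case against.** The strongest reply is that the harm is small where the plan expects the effect to lie.

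- At d = 0.32–0.44 coverage is not degraded, and at d = 0.40 the mean estimate is only 0.02–0.04 too high. This stands. The low coverage figures belong to effects below the range cited in 2.7.
- The article plans t-tests and ANOVA and mentions no confidence intervals. This stands, so coverage matters only if an interval is reported.
- Final-look type I error hardly moves. This stands. Counting significance at two looks is not something the plan proposes.
- The stated design analysis implies far fewer extensions, and the two-sided default prior does not fit it. The largest Bayes factor for H0 under that prior is 6.5 at 100 per arm and 9.0 at 200 per arm, so a boundary of 10 could not be reached for H0 in 45.5% of cases. Both parts are fair. The stated rates under H1 in fact match 200 per arm with one-sided priors (88.0% and 93.9%), not 200 people in total. If the first look were at 200 per arm, coverage at the effects checked would be about 91–98% and the mean estimate at d = 0.40 would be 0.401–0.406. The sizes above are therefore conditional on a start at 100 per arm.
- Section 2.6.1 lists at least eight primary measures, and an outcome that does not drive the extension is affected less. This stands. With an assumed correlation of 0.5 and the same true effect, the bias roughly halves (mean 0.41–0.42 at d = 0.40) and coverage is about 94–96%.
- Sequential detail can be left to an analysis plan. This does not answer the point: the article itself states a fixed-sample alpha and power and an open-ended stopping rule in one section, and they conflict as stated.

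**Conclusion.** The point holds in a limited form. The frequentist tests are justified at a fixed 200 completers, yet nothing keeps them there once the Bayes factor extends recruitment, so the stated alpha and power do not describe the test that would be run.

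A reader might infer more: that effects will always be overstated, that intervals generally cover only about 89%, or that alpha is clearly broken. The documents do not support this. Upward bias is modest at the design effect and absent at d of 0.10 or less. Coverage of 87–91% is a worst case at effects below the cited range of 0.32–0.64, for an interval the article does not mention. Type I error at the final look is about 2–7%.

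All sizes rest on an assumed look schedule, cap, prior side and single deciding outcome, and on a first look at 100 per arm. The inconsistency itself needs none of these assumptions. It should be corrected, and it does not invalidate the design.

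**What to change.** In 2.7 and 2.8, state that the frequentist t-tests are run once, on the planned 200 completers, and that this is the frequentist result whatever the Bayes factor shows. Students added by the extension enter the Bayes factor analysis. Any frequentist result from the extended sample is labelled descriptive or adjusted for the sequential rule.

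This restores the 5% alpha, an unbiased estimate and 95% coverage for any interval reported. It costs wording only. The downside is that the fixed-size result does not use the extension students, so it is less precise and has lower power than the naive final analysis, and after an extension the two approaches rest on different samples. Reporting the extended-sample t-test as descriptive or adjusted keeps the comparison visible.
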